## Abstract

**Background::**

Surgically assisted rapid maxillary expansion (SARME) generates an uncomfortable postoperative period accompanied by pain, edema, and paresthesia. There are few studies on the effect of photobiomodulation (PBM) after SARME and it was not possible to find studies on the efficacy of light emitted by diode (LED) after this type of intervention. The main objective of the study will be to evaluate the efficacy of PBM with LED in the control of pain, facial edema, paresthesia, and bone repair after SARME.

**Methods::**

A randomized, double-blind, placebo-controlled clinical trial involving 72 participants aged from 18 to 45 years, who search the Department of Buccomaxillofacial Surgery and Traumatology of Mandaqui Hospital Complex, will be conducted. Immediately after surgeries, the participant will be inserted into the placebo or LED group. In the LED group, the participants will receive PBM with an extraoral device (660 and 850 nm with 6 J per point) and an intraoral device (660 nm with 2 J per point) and in the control group the person in charge of the application will simulate the irradiation with the devices kept off. The applications will be in the immediate postoperative period, 1, 2, 7, 14, 30, 60, 90, and 120 days after the end of the surgeries, when the evaluations will also be performed. Facial measurements, extra and intraoral sensitivity, pain and bone repair will be evaluated. Secondarily, data regarding the occurrence of headache; otalgia; nausea; bruising; nasolacrimation; epistaxis; dysphagia; systemic and superficial temperature in the operated region; use of analgesics and anti-inflammatories; anxiety and impact of oral health on the participants’ quality of life will be computed.

**Discussion::**

Since PBM has shown positive effects on postoperative complications of other types of oral surgery and also has a positive effect on bone repair after maxillary disjunction, surgically assisted or not, it seems clear the need to evaluate its performance regarding pain, edema, and paresthesia after these surgeries.

**Trial registration::**

This protocol was registered in Clinical Trials platform (https://clinicaltrials.gov/) with the number NCT03814525, first published and last updated on January 24, 2019.

## Introduction

1

The transverse maxillary deficiency, or maxillary narrowing, is usually accompanied by the presence of a high arched palate, reduction of the arch perimeter and negative space, crowding and dental rotation, and unilateral or bilateral posterior crossbite.^[1]^ A variety of surgical techniques, including surgically assisted rapid maxillary expansion (SARME) and Le Fort segmental osteotomies are the most suitable surgical options for the treatment of transverse maxillary deficiency,^[2]^ supplemented by the use of expanders. The intraoperative complications of SARME are not frequent, but postoperative complications are more common, especially edema, pain and paresthesia of infra-orbital nerves, which can reach up to 30% of cases.^[3–6]^

Although these complications occur frequently, there are few data on the effects of photobiomodulation (PBM) on these outcomes after SARME. As PBM has shown positive effects on the postoperative complications of other types of oral surgery^[7,8]^ and also acts positively on bone repair after maxillary disjunction, surgically assisted or not,^[9–11]^ there is a need to evaluate its performance regarding pain, edema, and paresthesia after these surgeries. Added to this, SARME reach large anatomical areas that involve intra and extraoral structures. Thus, it also seems clear that there is a need to evaluate the performance of light emitting diode (LED) sources that can reach larger areas in the same application and combine wavelengths that are absorbed by shallower and deeper tissues.

The main objectives of this study are to evaluate the effects of PBM on pain, edema, paresthesia, and bone repair in the postoperative period of surgical maxillary disjunction in patients of a Buccomaxillofacial Surgery Department of a public hospital in the State of São Paulo (Conjunto Hospitalar do Mandaqui), in different experimental periods. Secondarily, data regarding the occurrence of headache; otalgia; nausea; bruising; nasolacrimation; epistaxis; dysphagia; systemic and superficial temperature in the operated region; use of analgesics and anti-inflammatories; anxiety and impact of oral health on the participants’ quality of life will be computed.

## Methods/design

2

### Study design

2.1

This randomized, double-blind, placebo-controlled clinical study will follow Resolution 466/2012 of the National Health Council, Brazil. The project was evaluated and approved by the Research Ethics Committee of Universidade Nove de Julho (process number 03645518030015511) and by Conjunto Hospitalar do Mandaqui Hospital (process number 03645518000005551) and was registered in the Clinical Trials platform (https://clinicaltrials.gov/) with the number NCT03814525, first published and last updated on January 24, 2019. Surgeries and treatment with the PBM will be performed at the Mandaqui Hospital Complex in the city of São Paulo, Brazil, during the period from January 2, 2019 to January 30, 2021.

The protocol is in accordance with the 2013 standard protocol items: recommendations for interventional trials (SPIRIT) statement. The SPIRIT checklist can be found as an additional file and Figure 1 is the SPIRIT figure. SPIRIT was developed to provide guidance in the form of a checklist of recommended items to include in a clinical trial protocol, to help improve its content and quality.

**Figure 1 F1:**
[figure not shown]
SPIRIT figure as recommended by the 2013 SPIRIT statement. SPIRIT = standard protocol items: recommendations for interventional trials.

### Participants

2.2

Participants of both genders, requiring surgical disjunction of the maxilla and that meet the eligibility criteria described below will be selected from the service of the Department of Buccomaxillofacial Surgery and Traumatology of Mandaqui Hospital Complex. After verbal explanation and reading about the procedures to be used in the study, patients who agree to participate will sign a free and informed consent term.

Inclusion criteria:

Transverse maxillary deficiency greater than 5 mm with bilateral posterior crossbite and indication for surgical maxillary disjunction;Agree to participate in the study after reading and signing the term of consent for participation in clinical research;Aged between 18 and 45 years.

Exclusion criteria:

Transverse maxilla deficiency, with unilateral posterior crossbite;Local or systemic alterations that contraindicate surgical intervention or hinder the postoperative period;Smokers;Display photosensitivity history;Possess systemic diseases, chronic pain, or neurological and psychiatric disorders;Have been using anti-inflammatories, analgesics, or bisphosphonates in the past 15 days;Pregnant;Breastfeeding;Participants who present any type of complication during surgery (hemorrhage, operative difficulty), as these cases will not be in the expected pattern for these surgeries. These data will not be part of the statistical analysis but will be described and discussed, as well as possible adverse effects.

### Experimental groups

2.3

Participants will be divided in 2 groups:

PBM group: the participants will receive PBM after surgery.Control group: participants will be attended to in the same way as the PBM group. The responsible for the application of the PBM will simulate the irradiations by positioning the devices in the same places as in the PBM group, but the equipment will be kept off. In order for the participant to not identify the group to which he/she belongs, the device activation sound (beep) will be recorded and switched on at the time of application.

### Sample calculation

2.4

To determine the number of participants in each experimental group, a sample calculation based on the variability of the results of 3 articles that evaluated the main outcomes of this study in similar situations was performed.^[12–14]^ Using the unpaired *t* test method ^[15]^ the required sample would be 66 individuals, 33 per group. Calculations were performed using a significance level of 0.05 (implying a 5% Type I error and resulting in a 95% confidence interval analysis) and an absolute error of 5%. Considering a 10% loss, a loss of 3 participants per group should be predicted, thus, 72 patients will be recruited, 36 per group.

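### Minor: 36 per group protects the required 33 for 3 losses per group (8.3% of those recruited), not for the 10% loss that section 2.4 names

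*Protocol article*

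**What the plan says.** The sample calculation in section 2.4 of the protocol article has two steps. The first, described as "Using the unpaired *t* test method" with a 5% significance level, gives the number needed for analysis: "the required sample would be 66 individuals, 33 per group". The second adds an allowance for attrition: "Considering a 10% loss, a loss of 3 participants per group should be predicted, thus, 72 patients will be recruited, 36 per group".

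The loss is therefore expressed in two ways, as a rate (10%) and as a count (3 per group), and the sentence treats them as the same thing. The recruited number, 36 per group, follows from the count. The abstract repeats the total of 72.

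**The concern.** A loss allowance answers one question: if this share of the people enrolled drops out, will the required number remain? The share must therefore be taken of those enrolled, and any fraction of a person should be rounded so that the requirement is kept. Here the 3 losses fit a 10% share of the smaller, evaluable number with the fraction dropped. Both choices lean the same way, and the recruited number comes out slightly short of what the stated rate needs.

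What is at stake is the accuracy of a stated design figure. As worded, a reader would take it that the trial can lose 10% and still have 33 per group, and in expectation it cannot. Paresthesia and bone repair are primary outcomes followed to 120 days (Outcome measures), so the attrition allowance bears on primary analyses. The size of the discrepancy is nevertheless very small.

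**Working it through.** **Inputs**, all from section 2.4: required evaluable number 33 per group (66 in total); loss rate 10%; loss count 3 per group; recruited number 36 per group (72 in total).

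**1. Reproducing the plan's figure.**
- 10% of the evaluable number: 0.10 × 33 = 3.3, taken as 3.
- Recruited: 33 + 3 = 36 per group, and 2 × 36 = 72.

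This gives the stated figures exactly. The article does not show the step, so the rounding of 3.3 to 3 is inferred from the result.

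**2. What rate do 3 losses represent?**
- Of those recruited: 3/36 = 8.3% (in total, 6/72 = 8.3%).
- Of those required: 3/33 = 9.1%.

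Neither base gives 10%.

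**3. What remains if 10% of those recruited are lost?**
- Per group: 36 × 0.9 = 32.4 expected, against 33; shortfall 33 − 32.4 = 0.6.
- In total: 72 × 0.9 = 64.8 expected, against 66; shortfall 66 − 64.8 = 1.2.

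**4. Cross-check from the requirement upward.**
- 33/0.9 = 36.7 recruits per group would be needed for an expected 33 after a 10% loss. This is above 36 by a fraction of a person, in agreement with step 3.

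**5. Whole participants.**
- One group: losing 3 of 36 (8.3%) leaves 33; losing 4 of 36 (11.1%) leaves 32.
- Both groups together: losing 7 of 72 (9.7%) leaves 65, below 66, at a rate still under 10%.

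The result of 33 per group cannot itself be rederived from the article, and this check does not need it. Only the step from 33 to 36 is examined.

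**The case against.** The best defence is that section 2.4 is consistent with its own count. It does not leave the loss as a bare percentage; it predicts 3 per group, and 36 − 3 = 33. On that reading the 10% is only a rough basis for the count, and the count is fully covered. This stands, and it is why the point is one of wording and not a failed calculation.

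A related defence is that people come in whole numbers. Within one group, the largest loss not exceeding 10% is 3, and that leaves 33. This also stands for a single group. It does not rescue the total: 7 losses among 72 are 9.7% and leave 65.

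It can also be said that any forecast of 10% is rounded, and that the gap between 8.3% and 10% is smaller than the uncertainty of the forecast. That is fair as a comment on consequence. It does not make the sentence correct.

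Three stronger readings are tempting, and the article supports none of them:

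- A reader might infer that a 10% loss leaves only 32 in each group. The expected number is 32.4, and actually ending with 32 of 36 means losing 11.1%.
- A reader might infer that the trial is underpowered. The article condenses the full protocol and gives no power, so no drop can be computed from it. Purely as illustration, if 33 per group gave 80% or 90% power (assumed; two-sided 5%, normal approximation), 32 per group would give 78.8% or 89.1%, a change of about one point.
- A reader might infer that the same 3 places must also absorb the participants removed for complications during surgery (section 2.2), since group envelopes are opened only after suturing (section 2.8). The article does not say whether the 72 counts patients before or after that exclusion, so this cannot be concluded.

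**Conclusion.** The point holds as a minor correction. The sentence equates a 10% loss with 3 participants per group, while 3 of the 36 recruited is 8.3%. If 10% of recruits are lost, the expected evaluable number falls short of the stated requirement by less than one participant per group and by a little over one in total.

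This conclusion takes 33 per group as given, applies the loss rate to those recruited, and assumes equal loss in the two groups. It does not depend on any assumed power, effect size or standard deviation. It does not show that the sample is inadequate and gives no reason to enrol more patients.

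**What to change.** Keep 72 and replace the loss sentence in section 2.4 with wording such as:

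*36 per group allows for 3 losses per group (about 8%); at 10% loss about 32 to 33 per group (about 65 in total) are expected to remain.*

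The cost is one sentence. The stated tolerance becomes slightly less favourable, and the number recruited, the allocation and the total in the abstract all stay as they are.

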### Randomization

2.5

To randomly distribute the subjects in the 2 experimental groups, a random sequence generator program (https://www.randomizer.org/tutorial/) will be used and the 6-member randomization option will be selected. Opaque envelopes will be identified with each number and inside it a sheet containing the information of the corresponding experimental group will be inserted according to the generated order. The envelopes will be sealed and will remain sealed in numerical order in a safe place until the time of the surgeries. The generation of the sequence and the preparation of the envelopes will be performed by a person who is not involved in the study.

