### Procedures to guarantee double blinding (patient and examiners) in the postoperative period

2.8

Once the suture is finished, the researcher responsible for applying PBM will remove and open the envelope containing the experimental group information in which the patient will be inserted and will proceed to the experiment. A single researcher will execute the PBM application and he/she will not perform any type of evaluation. The pre and postoperative evaluations will be done by 2 examiners who will not be aware of the group in which each patient is allocated. Participants will not be aware of whether or not they have received PBM, since the person responsible for the application will position the equipment in the irradiation locations in all participants and will only trigger the light when and where predicted in the specific experimental group. The characteristic sound of the device will be triggered by recording in the control group.

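### If the 6-member option means balanced blocks of 6, the fixed and published block size lets anyone who tracks every allocation deduce about a quarter of them, ahead of an undefined exclusion for operative difficulty

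*Protocol article*

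**What the plan says.** **Sequence.** Section 2.5 (Randomization) of the protocol article uses a web-based generator and states that "the 6-member randomization option will be selected". Section 2.4 (Sample calculation) sets the total: "72 patients will be recruited, 36 per group". Neither section uses the word block or gives a ratio within each set of 6.

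**Concealment.** Section 2.5 says the envelopes are opaque and numbered. "The envelopes will be sealed and will remain sealed in numerical order in a safe place until the time of the surgeries". Also: "The generation of the sequence and the preparation of the envelopes will be performed by a person who is not involved in the study".

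**Opening and delivery.** Section 2.8: "Once the suture is finished, the researcher responsible for applying PBM will remove and open the envelope". The same section adds: "A single researcher will execute the PBM application and he/she will not perform any type of evaluation". Its heading names who is blinded: "Procedures to guarantee double blinding (patient and examiners) in the postoperative period". Surgeons are not named there.

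**Exclusion.** The exclusion criteria in section 2.2 (Participants) include "Participants who present any type of complication during surgery (hemorrhage, operative difficulty". These cases are left out of the statistical analysis but are to be described and discussed. The section does not define operative difficulty, and does not say who decides or whether the decision is recorded before the envelope is opened.

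**Frequency.** The Introduction says that intraoperative complications of this surgery are not frequent.

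**The concern.** Sealed envelopes hide the current card. They do not hide what follows from the cards already drawn when the block size is constant and known. Once one arm of a block is used up, every remaining card in that block is certain. One person at one hospital opens every envelope and delivers light or sham, so that person holds the complete allocation history.

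This matters because of the step just upstream. A complication during surgery arises before the envelope is opened, and a judgement that the operation was difficult removes the patient from the analysis. Difficult operations plausibly lead to more pain, edema and nerve disturbance, which are primary outcomes. If the person judging difficulty knew or could guess the next arm, the choice to exclude or keep a patient could depend on it, and the comparison would be biased in a way that no later analysis could repair.

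**Working it through.** The document gives no figure for predictability. The only figures of its own to reproduce are the sample size, 33 + 3 = 36 per group and 2 x 36 = 72, and the fit of 6 into it, 72 / 6 = 12 complete sets.

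**Inputs**
- Block size 6, constant (section 2.5).
- 72 patients, 36 per group (section 2.4).
- 3:3 within each block: an assumption. The text does not state it; 72 = 12 x 6 and the equal groups support it.
- The observer knows every past allocation. By section 2.8 this holds for the PBM operator.

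**Step 1. Certain allocations in a 3:3 block.** There are C(6,3) = 20 equally likely sequences. An allocation is certain when one arm has no cards left.

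| Certain allocations in the block | Sequences |
|---|---|
| 1 | 12 |
| 2 | 6 |
| 3 | 2 |

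Mean = (12 x 1 + 6 x 2 + 2 x 3) / 20 = 30 / 20 = 1.5 of 6, or 25%. The closed form for n per arm agrees: 2n/(n + 1) = 6/4 = 1.5.

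Over 12 blocks: 12 x 1.5 = 18 of 72. In simulation, the 95% range for one trial was 14 to 23.

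**Step 2. Best guess.** The observer always names the arm with more cards left, and tosses a coin when they are equal. Expected correct guesses = n + 2^(2n-1)/C(2n,n) - 0.5. For n = 3: 3 + 32/20 - 0.5 = 4.1 of 6 = 68.3%, against 50% with no information.

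**Step 3. Alternatives**
- One permutation of 72 with n = 36. Certain: 72/37 = 1.95 patients (2.7%). Correct guesses: 36 + 2^71/C(72,36) - 0.5, about 40.8 of 72 = 56.7%.
- Varied block sizes, simulated for an observer who knows which sizes are possible but not their order. This is a cautious assumption, since the sizes would be withheld.

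| Scheme | Certain | Best guess correct |
|---|---|---|
| Fixed 6 | 25.0% | 68.3% |
| Random 4 or 6 | 5.4% (0 to 11 of 72) | 69.1% |
| Random 4, 6 or 8 | 2.3% (0 to 7 of 72) | 67.9% |
| One permutation of 72 | 2.7% | 56.7% |

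Varying the block size removes most of the certainty but leaves best guessing where it was. Only the single permutation lowers both.

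**Step 4. How often knowledge could meet the exclusion.** The document gives no complication rate. As an assumption, suppose that 5 to 10% of operations raise the question of exclusion. Certain knowledge would then coincide with that question in 18 x 0.05 = 0.9 to 18 x 0.10 = 1.8 patients, about 1 to 2 of 72. Best-guess knowledge adds some further exposure. Neither figure is a size of bias: whoever knows must also be, or inform, whoever decides.

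**The case against.** The case on the other side has four parts.

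1. **The reading is assumed.** The text states neither blocks nor a 3:3 split. If the sets of 6 are not balanced, the certain share falls toward zero. This stands as a condition on every number above. On that other reading the stated setting would not by itself assure 36 per group, so section 2.5 would still need clarifying.

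2. **The route to bias is not in the document.** The operator performs no evaluations and is given no part in enrolment, scheduling or exclusion. A reader might infer that surgeons see whether the device is lit after each operation and build up the history, or that operations could be reordered to suit the next arm. The document supports neither. It does not say that surgeons stay or keep count, section 2.7.2 has three surgeons, so none need see the whole sequence, and it says nothing on reordering the operating list. A reader might also infer that one unmasked patient would let an examiner work out others. Section 2.8 keeps both examiners unaware of allocation, and one known arm moves the chance that another member of the same block has the opposite arm only from 1/2 to 3/5. These inferences should not be part of the point.

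3. **The exclusion should be rare and visible.** Complications are called infrequent, and excluded cases are to be described, so selective exclusion would leave some trace. This stands, and limits the likely size.

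4. **Good safeguards exist.** Independent preparation, opaque numbered envelopes and opening after suturing are sound. They protect the current card but do not prevent deduction from a constant block size. Opening late does not help when the next arm is already certain.

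**Conclusion.** The point holds as a conditional vulnerability in a stated design choice. If the 6-member option means 3:3 blocks of 6, a person holding the full allocation history can deduce on average 18 of 72 allocations (25%) and guess 68% correctly. By the text that is the PBM operator; surgeons are not listed as blinded, but are not shown to hold the history either.

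A reader might go further and conclude that a quarter of allocations are known in advance to those who choose which patients stay in the trial. The document does not support that. It gives the operator no say in exclusion and does not state who decides or when. It does not rule the link out either. The 25% measures predictability, not bias, and no bias has been demonstrated.

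The change is still worth making: it alters one stated setting, costs very little, and lowers predictability ahead of a subjective decision that removes patients from the analysis.

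**What to change.** State in section 2.5 what the 6-member option means. Then have the independent person generate the list in one of two ways:

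- **Randomly varied block sizes**, withheld from the operator, surgeons and examiners. Certain allocations fall to about 2 to 5%; best guessing stays near 68%.
- **One random permutation of 72 with 36 per arm.** About 2 of 72 are certain and best guessing falls to about 57%. The price is possible modest imbalance over calendar time, and 36:36 holds only if all envelopes are used.

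Under either option, keep the block structure out of trial documents until recruitment ends. In sections 2.2 and 2.8, state who decides on intraoperative exclusion and by what criteria, and require the decision to be recorded before the envelope is opened. That record closes off exclusion after the arm has been seen; the change to the list limits what can be deduced beforehand, so both are needed.

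The cost is one generator setting and a few sentences. The sample size, visits and measurements do not change.
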